### Outcome measures

A summary of the outcome measures to be collected is shown in Table 3. Participants will attend four clinic visits throughout the study (baseline, 6, 12 and 18 months). All clinical testing will take place in the Department of Medicine at the University of Melbourne, Western Hospital, Footscray, with the exception of the blood collection and laboratory testing for routine biochemistry and hormonal measures which will be completed by an external pathology laboratory.

**Table 3 T3:** **Summary of the measures to be collected for the ****
*Osteo-cise: Strong Bones for Life *
****study**

**Variables**	**Data Collection Method**	**Data Collection Points**			
		**Baseline**	**6 months**	**12 months**	**18 months**
**Primary outcome measures**					
Hip and spine BMD	DXA hip and spine scan	x		x	x
Functional muscle power	Stair climbing test	x	x	x	x
**Secondary outcome measures**					
Muscle power	Leg press (3-RM)	x	x	x	x
	30 second sit-to-stand	x	x	x	x
Muscle strength	Leg press and lat pulldown (3-RM)	x	x	x	x
Muscle function and balance	Functional reach test	x	x	x	x
	Four-square step test	x	x	x	x
	Timed-up-and-go (TUG)	x	x	x	x
Anthropometry and body composition	Height and weight	x	x	x	x
	DXA lean mass and fat mass	x		x	x
Trabecular bone microarchitecture	MRI knee	x			x
Falls	Monthly falls calendars	Monthly calendar			
Adverse events	Monthly falls calendars	Monthly calendar			
Cost effectiveness	EuroQol (EQ-5D)	x	x	x	x
Quality of life	SF36 questionnaire	x	x	x	x
**Other measures**					
Diet	24-h food recall questionnaire	x	x	x	x
Lifestyle and medical history	Questionnaire	x	x	x	x
Biochemistry and hormonal	Serum 25-hydroxyvitaminD				
		x	x	x	x
	Parathyroid hormone (PTH)	x		x	x
	Routine biochemistry	x		x	x
Physical activity	CHAMPS questionnaire	x	x	x	x
Historical physical activity	Questionnaire	x			
Osteoporosis health beliefs and knowledge	Osteoporosis Knowledge Test (OKT)	x		x	x
Osteoporosis attitudes and prevention behaviours	Osteoporosis Health Belief Scale (OHBS)	x		x	x

#### Primary outcomes

The primary outcome measures will be changes in proximal femur and lumbar spine BMD and lower limb functional muscle power.

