### Sample size

In order to calculate the number of participants required for this study, power calculations were performed based on BMD and functional muscle power results from previous exercise intervention trials [37,39]. It was estimated that 60 participants in each group would provide at least 90% power to detect a 1.8% difference (assuming a standard deviation [SD] of 3.5) for the change in femoral neck BMD at p < 0.05 (two-tailed). For functional muscle power, we estimated that 24 participants would provide 90% power to detect a 15% difference for the change between the groups (two-tailed, P < 0.05) assuming a SD of 15%. Therefore with an anticipated 20% dropout rate, a minimum of 72 participants per group will be required (144 in total).

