##### *Bone mineral density (BMD)*

Areal bone mineral density (aBMD, g/cm^2^) will be measured at the lumbar spine (L1-L4) and proximal femur (total hip and femoral neck) using a Hologic Discovery W dual-energy X-ray absorptiometry (DXA) machine with the APEX Software v3.2 (Hologic, Bedford, MA). Standardized procedures for participant positioning and scan analysis will be used for all scans [40]. All follow-up measurements will be analyzed using the ‘comparison’ feature of the Hologic APEX 3.2 analysis program. The short term co-efficient of variation (CV) for repeated measurements of aBMD in our laboratory is 0.8% for lumbar spine, 0.8% for total hip and 1.5% for femoral neck aBMD.

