### Statistical analyses

Statistical analyses will be computed using STATA statistical software (version 11.0, Stata Corp, College Station, TX). Baseline and demographic data will be presented using descriptive statistics. All intervention data will be analysed according to the principle of intention-to-treat (ITT) and adjusted for multiple comparisons where appropriate. Non- normally distributed data will be transformed prior to analysis. Comparisons between the groups for all continuous primary and secondary outcomes variables will be made using repeated measures analysis of variance (ANOVA) for both time and group-by-time interactions. ANOVA or analysis of covariance (ANCOVA) will be used for absolute and/or percent changes after 12 and 18 months after adjusting for relevant confounders. Falls will be analysed according to the rate of falls per person-year, the proportion sustaining one or more falls and injurious falls during follow-up. The number of falls will be analysed using Poisson regression models with robust standard errors to allow for non-independence of multiple events for the same participant and negative binomial regression models allowing for overdispersion.

Cost utility analysis: Cost data is often skewed and thus not normally distributed. Therefore the Kruskal-Wallis one-way analysis of variance will be used to test the difference in cost and quality of life between the ‘usual care’ and exercise groups. To investigate the difference in cost between the groups, the transformed cost variable will be used as the dependent variable in a multivariable ordinary least square (OLS) regression model. All data will be presented as means ± SD or 95% CI unless stated. The significance level will be *p* < 0.05 or smaller where adjusted for multiple comparisons.

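### Four primary variables have no lead outcome, primary time or defined multiplicity family, and the sample size makes no allowance for the adjustment that the analysis section contemplates

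*Protocol article*

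**What the plan says.** The Primary outcomes section of the protocol article reads: "The primary outcome measures will be changes in proximal femur and lumbar spine BMD and lower limb functional muscle power". The Bone mineral density section says that BMD "will be measured at the lumbar spine (L1-L4) and proximal femur (total hip and femoral neck"). Together these give four primary variables: lumbar spine, total hip and femoral neck BMD, and stair-climb power. No order among them and no rule for declaring success is given.

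The Statistical analyses section compares groups on continuous outcomes by repeated measures ANOVA, with a group-by-time interaction. It adds that "ANOVA or analysis of covariance (ANCOVA) will be used for absolute and/or percent changes after 12 and 18 months". Results are to be "adjusted for multiple comparisons where appropriate", and the significance level is "0.05 or smaller where adjusted for multiple comparisons". It names no method, no family of tests and no primary time.

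The Sample size section makes two calculations. The first sets N: "It was estimated that 60 participants in each group" would give at least 90% power for a 1.8% difference (SD 3.5) "for the change in femoral neck BMD at p < 0.05 (two-tailed"). The second takes 24 participants for functional muscle power, with a 15% difference, SD 15%, 90% power and again two-tailed 0.05. The target becomes 72 per group after 20% dropout. Total hip and lumbar spine BMD have no calculation.

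**The concern.** The protocol leaves open which result decides the trial. Four variables share primary status, and the change analyses look at both the end of the supervised program (12 months) and the end of the translational phase (18 months). The analysis section foresees a level below 0.05 in some cases, but the sample size section does all its work at 0.05.

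The two ends of that choice have different costs. If adjustment is judged not to be appropriate, a trial of an ineffective program has well over a 5% chance of a positive primary result. If a simple split of the level is used, the femoral neck comparison that sets N loses power it cannot spare. A later analysis plan can name the method, but it cannot restore power at a fixed N. The choice of family therefore belongs with the sample size.

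**Working it through.** **Inputs.** From Sample size: femoral neck difference 1.8, SD 3.5, 60 per group, two-sided 0.05; stair-climb difference 15, SD 15; 72 per group with 20% dropout. From Primary outcomes and the BMD section: four variables. From Statistical analyses: change tests at 12 and 18 months. The documents give no correlations between outcomes or times, so those below are assumptions.

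**1. The plan's own femoral neck figure.**
- Standard error = 3.5 × √(2/60) = 0.639, and 1.8 / 0.639 = 2.817.
- Power at two-sided 0.05 ≈ Φ(2.817 − 1.960) = Φ(0.857) = 80.4%. The noncentral t gives 79.8%.
- For 90% power, n per group = 2 × (3.5/1.8)² × (1.960 + 1.282)² = 79.5, so 80. For 80% power the same formula gives 59.4, so 60.

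The stated 90% is not reproduced; 60 per group is the size for 80%. This shortfall exists before any adjustment.

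**2. The plan's stair-climb figure.** The standardised difference is 15/15 = 1. If 24 means per group, power is 92.4% (noncentral t), so the stated 90% is met. At 60 per group it exceeds 99.9%.

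**3. No adjustment: chance of at least one false positive.**
- Four independent tests: 1 − 0.95⁴ = 18.5%.
- Four tests, BMD sites correlated 0.3, 0.5 or 0.7 and stair-climb power uncorrelated with BMD (simulated): 18.0%, 16.9% and 15.4%.
- Eight tests, if both times are confirmatory: 1 − 0.95⁸ = 33.7% if independent; about 21-31% with the same site correlations and 0.5-0.9 between times.

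**4. Flat split: power at 60 per group (noncentral t).**

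| Two-sided level | Femoral neck BMD | Stair-climb power |
|---|---|---|
| 0.05 | 79.8% | over 99.9% |
| 0.025 (two outcomes) | 70.7% | 99.9% |
| 0.0125 (four outcomes) | 61.1% | 99.8% |
| 0.00625 (eight tests) | 51.5% | 99.6% |

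With 72 × 0.8 = 57.6 completers, taken as 57 or 58, femoral neck power is 77.7-78.4% at 0.05 and 58.3-59.3% at 0.0125. At 0.0125, 90% power would need 109 evaluable per group (normal approximation).

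**5. Holm over the two sized outcomes.** At 57 per group, stair-climb power at the first-step level of 0.025 is 99.9%. Once that test rejects, femoral neck BMD is tested at the full 0.05. Treating the two results as independent, femoral neck power is 0.9988 × 77.7% + 0.0012 × 68.2% = 77.7%, the same to one decimal as with no adjustment. At 60 per group it is 79.8%.

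**6. Holm over all four.** Once stair-climb power is rejected, the femoral neck level is at least 0.05/3 = 0.0167. Power there is 65.1% at 60 per group and 62.4% at 57. It is higher if total hip or lumbar spine BMD also rejects, but the documents give no effect sizes for those sites.

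**The case against.** The strongest reply is that the plan does contemplate adjustment. Naming the method and family is commonly left to the analysis plan, and a journal article condenses. That stands as far as it goes: the missing name of a method is not the point here, and inflation of the error rate is conditional on no adjustment being made.

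It is also true that success on any one outcome is nowhere stated to be enough, and that the repeated measures analysis gives one group-by-time test per outcome. Four is therefore the fair count, and eight is an upper one that applies only if the 12- and 18-month change tests are both confirmatory.

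A reader might infer that the sponsor cannot both adjust and keep its power. The documents do not support that. The drop to 61% belongs to a flat Bonferroni split over four, which the protocol never names. Holm over the two sized outcomes, or a fixed sequence starting with femoral neck BMD, costs that outcome little or nothing. Nor does multiplicity explain the gap between 90% and 80%; that is a separate error in the sample size calculation.

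What the reply does not remove is that the stated power assumes an unadjusted level, the analysis section allows for a smaller one, and nothing in the protocol (lead outcome, order or success rule) reconciles the two.

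**Conclusion.** The point holds in a limited form. The protocol has four unranked primary variables, no primary time and adjustment left to judgement, while two of the variables are sized at unadjusted 0.05.

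- With no adjustment, the family-wise error is about 15-18% for four tests under assumed BMD correlations of 0.3-0.7 (18.5% if independent), and higher if both times count.
- With a flat Bonferroni split over four, femoral neck power at 60 per group drops from about 80% to about 61%. Stair-climb power is unaffected in practice.

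These figures rest on the protocol's own effect sizes and SDs; the correlations and the Bonferroni split are assumptions. The trial would remain interpretable, but its primary claim is not defined until the family is. This should be settled before the data are analysed.

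**What to change.** Name 12 months, the end of the supervised program, as the primary time. State the confirmatory family and control it by Holm. There are two workable families:

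- **Two outcomes.** Femoral neck BMD and stair-climb power, both already sized. Femoral neck power stays at about 78-80%. Total hip and lumbar spine BMD become secondary.
- **Four outcomes.** Keep all three BMD sites and stair-climb power as primary, apply Holm over four, and restate femoral neck power at the adjusted level: about 61% at 0.0125, or about 65% at 0.0167 once stair-climb power has rejected, both at 60 per group.

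The two-outcome family is the simpler one, but which BMD sites stay primary is the sponsor's design choice. In either case, correct the stated 90% power separately, because Holm does not repair it.

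The cost is about two sentences in the outcomes and statistics sections. The downside is that the 18-month contrasts become secondary, as do total hip and spine BMD under the two-outcome family.

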##### *Bone mineral density (BMD)*

Areal bone mineral density (aBMD, g/cm^2^) will be measured at the lumbar spine (L1-L4) and proximal femur (total hip and femoral neck) using a Hologic Discovery W dual-energy X-ray absorptiometry (DXA) machine with the APEX Software v3.2 (Hologic, Bedford, MA). Standardized procedures for participant positioning and scan analysis will be used for all scans [40]. All follow-up measurements will be analyzed using the ‘comparison’ feature of the Hologic APEX 3.2 analysis program. The short term co-efficient of variation (CV) for repeated measurements of aBMD in our laboratory is 0.8% for lumbar spine, 0.8% for total hip and 1.5% for femoral neck aBMD.

##### *Functional muscle power*

Functional muscle power will be assessed by the Timed Stair Climb Test [41]. Participants will be instructed to climb a flight of stairs (10 steps, 14 cm rise per step) as quickly as possible without using the handrails or any other aid. Stair climbing power will be calculated according to the method described by Lazowski et al. [42].

(1)$$\text{SCP (W) = }\frac{\text{body weight }\left(\text{kg}\right)\text{ x gravity }\left({\text{ms}}^{-1}\right)\text{ x step height }\left(\text{m}\right)\text{ x no}.\text{ of steps}}{time(s)}$$

The short term co-efficient of variation for repeated measurements of this test in our laboratory is 2.2%.

#### Secondary outcome measures

The secondary outcome measures will include: changes in lower limb and back maximal muscle strength, power, balance and function, MRI-assessed distal femur and proximal tibia trabecular bone micro-architecture, body composition, falls incidence and health-related quality of life.

##### *Muscle strength and power*

Maximum muscle strength of the lower limbs and back will be estimated by three repetition maximum (3-RM) testing on a LC20 weights machine (GPI Bodyworx, Gym Co, Yarraville, VIC). A 3-RM test is the maximum weight that can be lifted for three complete repetitions of an exercise whilst maintaining good technique. The bilateral leg press exercise will be employed to determine maximal leg strength (knee extensors) and the seated row will be used to determine maximal back strength. The following formula used by Wathen et al. [43] will be used to predict each participant’s 1-RM, which represents the maximum weight that can be lifted for one complete repetition of an exercise:

(2)$$1\text{RM }=\;100\text{ x }\left[3\text{RM load}\right]/(48.8\;+\;53.{8\text{ xe}}^{(-}{}^{0.075\text{x}3)})$$

Peak muscle power of the lower limbs will be recorded on the bilateral leg press machine at five different loads (40%, 50%, 60%, 70% and 80% of the calculated 1-RM) by using the *Gymaware* power monitoring system (Kinetic Performance Technology, Canberra). Peak muscle power at each of the five loads will be assessed following the 3-RM testing and the calculation of 1-RM. All participants will complete two repetitions in succession at each 40%, 50%, 60%, 70% and 80% of their calculated 1-RM, with a 60 second rest between each test. Participants will be instructed to perform the concentric phase of the exercise as rapidly as possible but the eccentric (lowering) phase at a normal, controlled speed. For each test load, the highest peak power from the two repetitions and the corresponding velocity will be recorded.

##### *Muscle function and performance*

A series of commonly used functional tests will be used to assess lower limb function, dynamic balance and gait.

The *four square step test (FSST)* provides a measure of dynamic standing balance and stepping speed in four different directions [44]. To complete this test, participants will be required to step forward, sideways, and backwards over four canes resting flat on the floor in a cross formation, moving first in a clockwise direction and then counter-clockwise to return to the starting position. This test has been shown to have high interrater (ICC = .99) and retest reliability (ICC = .98) [44]. With a cut-off score of more than 15 seconds, the test has an 89% multiple faller sensitivity and 85% specificity for non-multiple fallers [44]. The test also has a positive predictive value of 86% for detecting a history of falls among community-living adults [44].

The *timed-up-and-go test (TUG)* is a measure of dynamic balance during three commonly performed functional activities: standing up and sitting down in a chair, walking and turning [45]. To increase the level of difficulty, participants will be asked to perform this test whilst simultaneously completing the cognitive task of counting backwards from 100 in 3's. This test has an established interrater reliability of ICC = .99 and prediction rate of 87% for identifying fallers and non-fallers when performing the test with an added cognitive task [46].

The *30-second sit-to-stand test* provides a measure of lower-extremity muscle strength where participants will be instructed to stand fully upright and then return to the seated position as many times as possible in 30 seconds [47]. This test has been shown to have good reliability with a test-retest intraclass correlation of 0.84 to 0.92 in a community-dwelling sample of older men and women aged 60 years and over [47].

The *functional reach test (FRT)* will be used to assess bilateral stance dynamic balance [48]. In this test, participants stand next to a wall unsupported and are asked to reach as far forward as possible without overbalancing. This test has been shown to be a valid tool with good interrater reliability (ICC = 0.98) and retest reliability (ICC = 0.92) [48] and has been shown to discriminate between healthy older people and Parkinson’s disease patients who were fallers and non-fallers [49,50].

##### *Trabecular bone micro-architecture*

All participants will be invited to have a Magnetic Resonance Imaging (MRI) scan of the left knee at baseline and 18 months to assess the effects of the intervention on trabecular bone micro-architecture at the distal femur and proximal tibia. MRI of the left knee will be acquired on a 3.0 T MR scanner (General Electric, Milwaukee, WI) using an eight-channel phased array knee coil (General Electric Medical Systems, WI). Images will be acquired with an axial 3D, phase cycled, fully balanced, steady-state coherent imaging pulse sequence (3D FIESTA-C), utilising the following parameters: repetition time ~11.8 ms, echo time 1.0 ms, flip angle 60 degrees, resolution 0.195 × 0.195, 512 × 384 matrix, slice thickness 1 mm and a scanning time ~16 minutes. A total of 50 slices will be acquired with a field of view of 10 cm.

Analysis of trabecular bone micro-architecture outcomes will be performed using an interface description language (IDL)-based image software program (RSI, Boulder, CO). Image processing consists of five steps including coil sensitivity correction, trabecular region segmentation, manual region adjustment, registration and bone/marrow thresholding, as described in detail by Newitt et al. [51]. The bone/marrow binary images will be generated by calculating a global threshold based on a dual reference limit and assuming a biphasic model [52]. These processed images will then be analysed for apparent structural parameters slice by slice (in 2D), similar to a previously described processing method [53]. For the distal femur, a 30 mm (30 slice) region of interest (ROI) will be analysed starting 5 mm from the most distal point of the femur. For the proximal tibia, a 15 mm (15 slice) ROI will be analysed starting 5 mm from the bone’s most proximal point. Within each axial image (or slice), the ROI will be selected consisting only of trabecular bone and marrow, with a border approximately 2 mm from the inner edge of the cortical bone boundary. Outcome variables after analysis will include: apparent bone-volume over total-volume fraction (BV/TV), apparent trabecular separation (TbSp), apparent trabecular plate thickness (TbTh) and apparent trabecular plate number (TbN) calculated for each slice.

##### *Falls incidence and adverse events*

Falls and adverse events, including fractures, will be ascertained using specific monthly ‘falls calendars’. A fall will be defined as “*unintentionally coming to the ground or some lower level and other than as a consequence of a sudden onset of paralysis, epileptic seizure, or overwhelming external force*” [54]. Participants will be instructed to document any fall and what, if any, medical attention was sought (doctor or hospital visits). At the end of each month participants will return their calendars via reply paid postage envelopes. If a fall is recorded, the participant will be contacted for further details. Any missing calendars will be followed up by research staff. Any injuries, incidents or adverse events that occur during *Osteo-cise* training sessions will be documented by the trainers in an Incident Report Form located in the *Osteo-cise* gym folder.

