##### *Cost Utility Analysis (CUA)*

The CUA will determine the quality of health outcomes averted by the *Osteo-cise: Strong Bones for Life* program. The outcome will be expressed as a cost per quality-adjusted life-years (QALYs) gained. This method of cost analysis involves an assessment of incremental change in health-related quality of life and the monetary costs related to the development and implementation of the *Osteo-cise* program as well as monetary costs related to any adverse events such as injury. The change in quality of life between the groups will be calculated using the difference in QALYs from baseline to the 12-month time point and will be determined using the EuroQoL-5D questionnaire [56].

The EuroQoL-5D considers five dimensions of health, including mobility, self-care, usual activities, pain/discomfort and anxiety/depression. The responses will be scored/weighted using recently published algorithms for Australia [57]. The assessment of monetary costs will include an incremental cost related to program development plus the costs of implementing the program including staff time and costs of all materials/equipment. Costs related to injury or adverse events will also be included (medical care, non-medical care and indirect costs). The Australian Medicare Scheduled fees will be used as uniform unit costs where applicable.

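### The named adverse-event source has a stated instruction and follow-up trigger for falls alone, and only the exercise arm adds trainer reports, so non-fall events and their costs may be captured unequally

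*Protocol article*

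**What the plan says.** The section Falls incidence and adverse events opens by giving the calendar a broad role: "Falls and adverse events, including fractures, will be ascertained using specific monthly" falls calendars. Table 3 agrees, with a separate row under secondary outcomes: "Adverse events Monthly falls calendars". No other method is listed there.

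The same section then says how the calendar is used. The instruction is: "Participants will be instructed to document any fall and what, if any, medical attention was sought". The follow-up rule is: "If a fall is recorded, the participant will be contacted for further details". Missing calendars are chased.

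A second route follows. "Any injuries, incidents or adverse events that occur during" Osteo-cise sessions "will be documented by the trainers in an Incident Report Form". The Osteo-Instruct section likewise asks trainers to record injuries or adverse events resulting from the sessions. The Self-management control group section gives controls the same testing but no structured program, and so no trainers or sessions.

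The Cost Utility Analysis section adds: "Costs related to injury or adverse events will also be included", covering medical, non-medical and indirect costs. Statistical analyses plans a test of the cost difference between the groups.

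**The concern.** The calendar is given an adverse-event role that its stated instruction and follow-up rule do not fulfil. A muscle strain or a painful joint without a fall is not something the participant is said to be asked to write down, and it would not prompt a call. In the exercise arm the same event, if it happens in a session, has a second recorder.

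Non-fall musculoskeletal injury is a foreseeable harm of a program with rapid resistance work and impacts that Table 2 rates up to about 6–9 times body weight, and safe translation to the community is one of the study's motives. The cost-utility analysis is the most exposed. Of the cost components it lists, program development and delivery fall on the exercise arm, while injury and adverse-event costs also arise in controls. If non-fall events are under-recorded in controls and better recorded in the exercise arm, the incremental cost is overstated.

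**Working it through.** No figure in the protocol bears on this point, so there is none to reproduce. The check is of which route covers which event.

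**Routes by type of event**

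| Event | Exercise arm | Control arm |
|---|---|---|
| Fall, and care sought for it | Calendar, with follow-up contact (plus trainer form if in a session) | Calendar, with follow-up contact |
| Fracture | Calendar (named source) | Calendar (named source) |
| Non-fall event during or resulting from a session | Calendar in principle, no stated instruction or contact; plus trainer report | Does not arise |
| Other non-fall event | Calendar in principle, no stated instruction or contact | Calendar in principle, no stated instruction or contact |

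The arms differ in the third row. Both arms also complete a lifestyle and medical history questionnaire at baseline, 6, 12 and 18 months, but it is not named as a source of adverse events or costs.

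**How complete is the trainer route?** From the Osteo-cise exercise section, at three sessions a week over 52 weeks:
- Planned sessions: 52 × 3 = 156.
- Supervised: 4 × 3 = 12 in the adoption phase. Each of four mesocycles adds 3 in its first week and 11 in the other weeks, so 4 × 14 = 56. Total 12 + 56 = 68.
- Without the scheduled trainer: 4 × 11 × 2 = 88, or 88/156 = 56%.

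Trainers therefore cannot be assumed to see every session event.

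**Illustration, on assumptions only.** Let the true non-fall event rate be equal in both arms. Let c be the share that calendars capture in either arm, and s the share of exercise-arm events that trainers record. If both sources are pooled, the apparent exercise-to-control ratio is

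[s + (1 − s)c] / c.

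| c | Ratio at s = 0.3 |
|---|---|
| 0.10 | (0.3 + 0.07)/0.10 = 3.7 |
| 0.25 | (0.3 + 0.175)/0.25 = 1.9 |
| 0.50 | (0.3 + 0.35)/0.50 = 1.3 |
| 0.75 | (0.3 + 0.525)/0.75 = 1.1 |
| 1.00 | 1.0 |

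At c = 0.25 the ratio is (0.1 + 0.225)/0.25 = 1.3 for s = 0.1 and (0.5 + 0.125)/0.25 = 2.5 for s = 0.5. The distortion vanishes if calendars capture every non-fall event (c = 1) or if trainer reports stay out of the comparison (s = 0). In the latter case, capture is equal but possibly thin. The documents give neither c nor s.

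**The case against.** The strongest reply is that the calendar is a stated route for adverse events in both arms, in the text and in Table 3. That the participant is told to record falls and nothing else is an inference: the protocol does not say so, and a condensed article may omit a calendar field for other events. This stands, and it rules out saying that controls have no route at all. It does not dispose of the point, because the article does spell out the instruction and the contact trigger, and both concern falls.

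A reader might also infer that trainers record all injuries in the exercise arm. The documents do not support that: the trainer route is limited to events during or resulting from sessions, and more than half of the planned sessions in the first year take place without the scheduled trainer. Exercise-arm events unrelated to sessions have no better stated capture than those of controls.

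Nor is a biased test actually planned. Statistical analyses specifies none for adverse events, the prose list of secondary outcomes leaves them out, and nothing says that trainer forms will be pooled with calendars or used for costing. Table 3 points to calendars alone. This stands too, and makes the bias conditional. What remains is that injury and adverse-event costs enter a between-group analysis with no stated rule on which source supplies them.

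Finally, recording session injuries is proper safety monitoring. The concern is with using those records in a comparison that has no counterpart in controls.

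**Conclusion.** The concern holds in a limited form. The stated instruction and follow-up trigger are narrower than the adverse-event role given to the calendar, and one arm has an extra recording route. Non-fall adverse events and their costs may therefore be captured unequally, probably to the disadvantage of the exercise arm, if trainer reports enter the between-group comparison or the cost-utility analysis.

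It would go too far to call the whole safety comparison one-sided, since falls, care sought for falls, and fractures have the same named source in both arms. The size is unknown. The ratios of 1.0 to 3.7 show how the mechanism works under assumed capture rates and are not estimates. Applying an assumed injury rate to the 72 participants per group would only count assumed events and would not measure bias. The change is still worth making before data collection, because events that were never asked about cannot be recovered at analysis.

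**What to change.** In Falls incidence and adverse events:
1. Have the monthly calendar in both arms ask about any injury or adverse event and any medical attention sought, and make any such entry trigger the same follow-up contact as a fall.
2. State that between-group adverse-event summaries, and the injury and adverse-event costs in the cost-utility analysis, use calendar data collected identically in both arms.
3. State that trainers' incident forms are reported separately, as descriptive session-safety data for the exercise arm.

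The cost is one more calendar item, somewhat more follow-up calls by existing staff, and an ethics notification. No session-safety information is lost. If the calendar already carries such an item and follow-up, a sentence saying so settles the first step; the second and third still need stating.
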